**DEMOGRAPHIC DATA**

| **Interview Date** | **Interviewer Initials** | | **Participant ID** |
| --- | --- | --- | --- |
| **Surname** | **First Name** | | **Other Names** |
| **Date of Birth:** ___ - _____ - ____ dd - mmm - yyyy  **Age** years | | | **Gender** (circle one)  **Male Female** |
| **Current Residence**  District _______________________________  Chiefdom/ Ward _______________________  Village________________________________ | | **Previous Residence**  District _______________________________  Chiefdom/ Ward _______________________  Village________________________________ | |
| **Marital Status:** Single Married Divorced Widowed | | | |
| **Cell Phone Number** | | | **Cell Phone Number of Caretaker** |
| **Occupation** (circle all that apply)  Health worker Traditional healer Traditional birth attendant Community/religious leader  Animal Farmer Crop Farmer Butcher Hunter Cook Cleaner  Labourer Trader Teacher Professional/Business Student  Child/Pupil Housewife Retired Unemployed  Other_____________________________(specify) | | | |

**OTHER MEDICAL CONDITIONS**

| Do you have any chronic illness? Yes No |
| --- |
| If Yes, name of illness(es), or main symptoms |
| Are you an Ebola survivor? Yes No |
| If Yes, please provide date of discharge |
| During the last 12 months have you been diagnosed with Malaria? Yes No |
| Are you currently pregnant? Yes No  Have you given birth to a child within the last year? Yes No |

**LASSA FEVER EXPOSURE SINCE DISCHARGE**

| **Do you think you may have been sick with Lassa Fever again since you were discharged from hospital?**  **Yes No** | |
| --- | --- |
| **If Yes, please describe symptoms and dates** | |
| **If yes, how do you think you were infected in this new illness?**  (circle one) | 1. Contact with rodents or rodent droppings in or near your household/compound 2. Contact with rodents or rodent droppings in another location 3. Eating contaminated food 4. Hunting rodents/small animals 5. Preparing rodents/small animals for cooking 6. Caring for someone who was ill 7. Contact with someone who was ill but not in your care 8. Witchcraft / Curse 9. Other (describe) 10. Don’t know |
| Has anyone within your household had Lassa Fever since you were discharged from hospital?  Yes No | |
| If Yes, please describe symptoms and dates | |
| Do you know anyone outside your household who got Lassa Fever since you were discharged?  Yes No | |
| If Yes, did you have contact with them?  Yes No | |
| If Yes, please describe symptoms and dates of the person who was ill | |
| Have you made any changes in your household or practices to prevent Lassa infections since you were discharged from hospital?  Yes No | |
| If Yes, please describe | |

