## 2.1 Host & transmission

The natural host for LASV is the common African soft-furred rat, *Mastomys natalensis*, in which infection is thought to be lifelong and harmless. Recently there have been reports of other host rodents and investigations into this are continuing.^9^ Viral transmission occurs - via aerosol or contact - from infected rats or their excretions to humans, and subsequent LASV infection in humans can be lethal. The virus can also be transmitted between humans via blood and tissue fluids, particularly in hospitals with weak infection prevention control measures, and among contacts exposed to body fluids through caring practices, resulting in high mortality rates.^3, 10^

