# Aims and objectives

The aim of this study is:

- To develop and examine the validity of a new assay to measure evidence of LASV infection for use with oral fluids by comparing naturally acquired antibody responses to LASV in oral fluids and blood serum samples from LF survivors and unexposed controls.

The specific objectives are:

1. To complete the development of a novel ELISA to investigate naturally acquired antibody responses LASV infection in non-invasive oral fluid samples
2. To validate this tool and determine its sensitivity and specificity by measurement of LASV-specific antibodies in oral fluids and blood samples from LF survivors and unexposed controls
3. To evaluate the feasibility of oral fluid as an alternative sampling tool using these findings
4. In LF survivors, to correlate LASV-specific antibody responses with time since clinical infection, original clinical characteristics and potential re-exposure events.

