## Data collection

Data will be collected using a study-specific questionnaire (Appendix 2), participants’ medical records during admission to KGH Lassa Fever Unit, and data held in the Survivors Study database. Variables for survivors will include demographics, symptoms and clinical information at the time of admission, dates of LF onset and discharge, laboratory test results at discharge, and information on any known exposure to LASV or LF patients since recovery, in order to explore potential immunity-boosting events.

Unexposed participants will be asked a series of questions regarding exposure to LASV hosts and/or cases to determine if they fulfil the inclusion criteria, and if not excluded based on responses, will be asked to respond to a brief demographic questionnaire.

Both groups will be asked to give feedback on using the oral fluid swab, including perceptions of the method as a follow-up and research tool.

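### The survivor questionnaire records rodent contact since discharge only as the perceived cause of a suspected second Lassa illness, so the re-exposure part of objective 4 is at risk of under-capture

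*Protocol*

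**What the plan says.** Objective 4 (Protocol, Aims and objectives) is "to correlate LASV-specific antibody responses with time since clinical infection, original clinical characteristics and potential re-exposure events". The Data collection section lists, among the survivor variables, "information on any known exposure to LASV or LF patients since recovery, in order to explore potential immunity-boosting events". Section 4.4 gives the study-specific questionnaire the task of covering exposures that might boost antibodies.

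The block of the survivor questionnaire on exposure since discharge is built as follows:

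- **Filter, asked of all:** "Do you think you may have been sick with Lassa Fever again since you were discharged from hospital".
- **Only after a yes:** "If yes, how do you think you were infected in this new illness". One answer is to be circled. Rodents or droppings around the home or elsewhere, hunting, and preparing animals for cooking are options here and nowhere else in the block.
- **Asked of all:** "Has anyone within your household had Lassa Fever since you were discharged from hospital" and "Do you know anyone outside your household who got Lassa Fever since you were discharged", the latter with a follow-up on contact.
- **Asked of all:** a yes/no item with free text on changes made to prevent Lassa infection.

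The similar list of causes under Lassa fever history concerns the illness that led to admission, not the time since discharge.

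Section 2.1 describes transmission "from infected rats or their excretions to humans", and also between humans. The Introduction says that most infections in endemic settings are believed to be sub-clinical or mild.

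**The concern.** Re-exposure has two sources in this protocol, infected rodents and infected people. The form asks every survivor about people, but about rodents only those who suspect a second illness. A survivor who has lived among rodents since discharge and stayed well leaves no direct trace of it. If infection often passes unnoticed, a filter on perceived illness removes the very exposures that a boosting analysis is meant to find.

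Recording would also depend on illness. A survivor noted as rodent-exposed would be one who believes they fell ill again, so rodent contact and a suspected second illness could not be told apart. Even those who pass the filter give one believed cause rather than a list of exposures. No later analysis can recover answers that were never collected.

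**Working it through.** **The plan's own figure.** The protocol gives no figure for objective 4. Its only sample size calculation is Table 1, for sensitivity: n = z²(1−p)/(p·e²). With z = 1.96, p = 0.85 and relative precision e = 0.10, n = 3.84 × 0.15/(0.85 × 0.01) = 67.8, rounded up to 68. The other 15 cells also reproduce. The present point does not touch that calculation.

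**Tracing the data items.** Each part of objective 4 against what is collected:

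- Time since infection: onset and discharge dates, no filter.
- Clinical characteristics of the admission: symptoms, severity and records, no filter.
- Re-exposure to human cases: household case and contact with an outside case, asked of all.
- Re-exposure to rodents: only behind the second-illness filter, one answer, as a perceived cause.

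Only the last item fails to match the Data collection section.

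**What that could do to the comparison.** This is an illustration; none of its inputs is in the documents except the 70 survivors. Let q be the share of survivors with rodent re-exposure and s the share of those whom the form captures. Assume no false positives, a two-sided 5% test, 80% power, and that a skipped item is read as unexposed.

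- Classed as exposed: n1 = 70·q·s.
- Share of the true mean difference that remains: R = (1−q)/(1−q·s), because the group classed as unexposed contains the missed exposed.
- Detectable true difference in SD: (1.960 + 0.842)·√(1/n1 + 1/(70−n1))/R.

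For q = 0.5 and s = 0.1: n1 = 3.5; R = 0.5/0.95 = 0.53; detectable difference = 2.802 × √(1/3.5 + 1/66.5)/0.526 = 2.92 SD. With full capture it is 2.802 × √(1/35 + 1/35) = 0.67 SD.

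The range, as R / detectable SD:

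| q | full capture | s = 0.05 | s = 0.10 | s = 0.30 | s = 0.50 |
| --- | --- | --- | --- | --- | --- |
| 0.3 | 1 / 0.73 | 0.71 / 3.88 | 0.72 / 2.72 | 0.77 / 1.52 | 0.82 / 1.14 |
| 0.5 | 1 / 0.67 | 0.51 / 4.18 | 0.53 / 2.92 | 0.59 / 1.59 | 0.67 / 1.16 |
| 0.8 | 1 / 0.84 | 0.21 / 8.20 | 0.22 / 5.68 | 0.26 / 2.98 | 0.33 / 2.05 |

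The normal approximation is rough where only a few survivors are classed as exposed. If skipped items were treated as missing instead, the comparison would shrink to survivors who suspect a second illness: 3.5 of 70 if 5% do, 35 of 70 if 50% do.

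**The case against.** The strongest reply is that the appendix form is not the only source. Section 4.4 draws risk factor information from admission records and the Survivors Study database, the Data collection section names that database again, and section 2.4 embeds this study in it. Its variables are not listed, so it may hold rodent exposure since discharge. This stands, and the point is conditional on it. It does not dispose of the point: no such variable is named, section 4.4 assigns boosting exposures to this questionnaire, admission records cannot hold events after discharge, and information already given to the Survivors Study may stop short of the sampling date.

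The form also records occupation (including hunter and farmer) and residence for everyone. These are coarse proxies and do not measure rodents in the home. The prevention item records changes in practice, not exposure.

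If rodent contact is nearly universal in a hotspot district, a plain yes/no item asked of all would give little contrast either. That is fair, and is a reason to ask about frequency and recency.

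The Introduction itself says that the evidence on the share of sub-clinical infection is thin, and it does not speak of reinfection in survivors. The argument from silent infection is therefore plausible rather than established.

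Finally, assay validation is the study's aim, and re-exposure is one part of the last objective, to be explored. That limits the weight of the point but does not remove it.

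**Conclusion.** The point holds in limited form. As written, the questionnaire does not directly ask about rodent contact since discharge in survivors who report no second illness, and so falls short of what the Data collection section promises. The rodent side of the re-exposure analysis is at risk of serious under-capture tied to perceived illness, unless the Survivors Study database supplies the data. Over the assumed ranges, 21% to 82% of a true difference would remain, and the detectable difference would be 1.1 to 8.2 SD against 0.67 to 0.84 SD with full capture. These figures show the direction and possible scale; they are not estimates for this study.

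A reader might infer more than the documents support:

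- That objective 4 cannot be answered. Its time and clinical parts and human-case contact are collected without a filter.
- That the form misses the main route of infection. Section 2.1 names the rat as natural host but does not rank the routes.
- That almost all survivors would be misclassified. If half of 70 were exposed, 5% reported a second illness independently of exposure, and skipped items were read as unexposed, 35 − 1.75 = 33.25 of 70 would be wrong, about 47%. The implied 5% capture merely restates the assumed second-illness rate.
- That waning would be underestimated. This needs boosting to occur and to accumulate with time, which the protocol does not state, and the Data analysis section plans only to describe antibody levels over time.

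**What to change.** Before data collection, do one of two things.

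- Add items for every survivor, placed before and apart from the second-illness question and allowing several answers, on rodent contact or droppings in or near the home, hunting, and preparing or eating rodents since discharge. Record frequency and most recent time for each.
- Or name, in the Data collection section, the Survivors Study variables that hold this information, and confirm that they run up to the date of sampling.

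The existing perceived-cause item can stay as it is. The cost is one or two extra questions within the one-hour visit, with no extra samples and no change in sample size.

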**LASSA FEVER HISTORY**

| **Duration of symptoms before admission to hospital?**  1-3 days 4-7 days 8-14 days 15-21 days 22-28 days >28 days | |
| --- | --- |
| **Symptoms at admission?**  (Circle all numbers that apply) | |
| 1. Fever | 1. Muscle and/or joint pain/ache |
| 1. Fatigue (general body weakness) | 1. Sore throat or pain with swallowing |
| 1. Headache | 1. Hiccups |
| 1. Loss of appetite | 1. Red eyes |
| 1. Nausea or Vomiting | 1. Blurry vision |
| 1. Abdominal pain | 1. Bleeding gums |
| 1. Diarrhoea | 1. Miscarriage |
| 1. Blood in the stool | 1. Other (please describe) |
| **Severity of illness at admission** (Circle one): Mild Moderate Severe | |
| **Do you think you know how you got sick?**  (circle one) | 1. Contact with rodents or rodent droppings in or near your household/compound 2. Contact with rodents or rodent droppings in another location 3. Eating contaminated food 4. Hunting rodents/small animals 5. Preparing rodents/small animals for cooking 6. Caring for someone who was ill 7. Contact with someone who was ill but not in your care 8. Witchcraft / Curse 9. Other (describe) 10. Don’t know |
| **When were you discharged from hospital?** ___ - _____ - ____ **dd – mmm - yyyy** | |
| **Laboratory results on discharge** | |

**PERCEPTION OF ORAL SAMPLE COLLECTION**

| Do you prefer giving a sample using the oral swab or do you prefer blood sample collection?  Oral Fluid Blood sample |
| --- |
| Do you think you would be happy to give an oral fluid sample every 2-4 weeks if you were part of a research study? Yes No |
| Any other comments/feedback about using the oral swab? |

**CONTROL PARTICIPANT ELIGIBILITY CHECK**

**For ‘Not eligible’ responses: do not recruit into the study; no further questions, no sample collection.**

| **Were you ever tested for Lassa Fever?** (circle one) **Yes No** | |
| --- | --- |
| **What was the final result of your test for Lassa Fever?** (circle one)  **Negative**  **Didn’t receive result (Not eligible) Don’t remember (Not eligible) Positive (Not eligible)** | |
| **Have you ever lived, worked or visited in a Lassa-endemic area? Yes (Not eligible) No** | |
| **Has anyone within your household had Lassa Fever? Yes (Not eligible) No** | |
| **Do you know anyone outside your household who got Lassa Fever? Yes No** | |
| **If Yes, did you have contact with them? Yes (Not eligible) No** | |
| **Temperature: (°C)** | **If above 37.5°C – Not eligible for study participation, no further questions and no sample collection. Advise individual to seek medical advice** |

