# Introduction

Lassa Fever (LF) is a viral haemorrhagic illness endemic in parts of West Africa including Sierra Leone, Liberia, Guinea, Mali and Nigeria where the illness was first identified.^1^ In endemic settings, it is believed that the majority of those infected with Lassa virus (LASV) experience sub-clinical infection or mild disease with only around 20% infections resulting in hospitalisation.^2^ Overall mortality from infection is thought to be ~1% but in hospitalised cases, case fatality rates of up to 50 to 70% have been reported,^3^ often linked to late presentation. LF outbreaks can cause significant public health emergencies, often triggered by patients presenting in health facilities that are unaccustomed to receiving haemorrhagic fever cases, with the accompanying risks of health worker and nosocomial infection, as well as the burden of investigating and managing large numbers of suspect cases.

During clinical LASV infection, early symptoms may include fever, headache, and muscle aches, mimicking symptoms of diseases such as malaria and typhoid fever which are common in LASV endemic areas. As clinical infection progresses, patients may go into shock, develop multi-organ failure, and sometimes bleed from the mouth, nose, eyes, or rectum.^4^ In addition, there is evidence that LF survivors suffer long-term sequelae such as hearing loss, depression, joint pain and hair loss.^3^ There are currently no vaccines to prevent LF nor approved drugs to treat, and although accepted wisdom is that early clinical use of the nucleoside drug ribavirin can reduce mortality in clinical cases, there is little scientific evidence to support this.

It is estimated that up to 300,000 LASV infections occur annually resulting in 5,000 deaths,^2^ but these data are based largely on the results of a single study carried out in the 1980s.^5^ Similarly, there is little evidence for the 20-80% proportions cited for sub-clinical and clinical disease. The need for more robust estimates based on up-to-date data has been recently emphasised by WHO in its Research & Development Blueprint which identified LASV as one of eight priority diseases for urgent attention.^6^ More precise estimates of these parameters, and deeper understanding of the exposure and immune status of populations in the endemic countries, will also be critical to developing, targeting, and evaluating the efficacy of LASV vaccine candidates and other control measures.

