# Methods

## 4.1 Recruitment

**Inclusion Criteria**

For LF survivor participants

- History of LF as documented by a positive anti-LASV Ag or IgM ELISA in the KGH diagnostic laboratory
- Age ≥6 years
- No fever at recruitment (Temperature below 37.5^o^C)
- Willingness to provide informed consent (or assent, if applicable)
- Willingness to undergo phlebotomy for blood samples and provide oral fluid samples

For unexposed control participants

- No history of LF clinical illness and/or LASV positive test,
- No history of residence, work or visiting in LF endemic zones
- No history of contact with a LF case
- Age ≥6 years
- No fever at recruitment (Temperature below 37.5^o^C)
- Willingness to provide informed consent (or assent, if applicable)
- Willingness to undergo phlebotomy for blood samples and provide oral fluid samples

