## 4.2 Study participants

Up to 70 LF survivors admitted to the KGH Lassa Ward for treatment of confirmed LF and discharged up to 15 years prior to the start of this study will be recruited. The study team will work with LF programme outreach staff at KGH to identify LF survivors and implement the study protocol.

Unexposed controls will be recruited from among individuals understood to have no exposure to the *Mastomys natalensis* rodent or LF cases. After agreement with the relevant authorities, control participants will be sought from among medical and/or nursing students in Freetown (an area considered outside the LASV endemic zone) as a relatively easily-accessed cohort of individuals for whom taking part in a research study may be of interest. The study brings no inherent benefit to participants, however those involved in study for health care/public health careers may benefit from taking part in a well-conducted research study. We will also collaborate with college authorities to offer lectures on the conduct of research studies and on LF as one of Sierra Leone’s priority emerging disease issues. A questionnaire including past travel/residence/contact information will be used to exclude candidates with possible exposure (Appendix 2: Control eligibility check).

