**CONTROL PARTICIPANT QUESTIONNAIRE**

**DEMOGRAPHIC DATA**

| **Interview Date** | **Interviewer Initials** | | **Participant ID** |
| --- | --- | --- | --- |
| **Surname** | **First Name** | | **Other Names** |
| **Age _______** years **Date of Birth:** ___ - _____ - ____  dd - mmm - yyyy | | | **Gender** (circle one)  **Male Female** |
| **Current Residence:**  District _______________________________  Chiefdom/ Ward _______________________  Village________________________________ | | **Previous Residence:**  District _______________________________  Chiefdom/ Ward _______________________  Village________________________________ | |
| **Marital Status:** Single Married Divorced Widowed | | | |
| **Cell Phone Number:** | | | **Cell Phone Number of Caretaker:** |
| **Occupation** (circle all that apply)  Health worker Traditional healer Traditional birth attendant Community/religious leader  Animal Farmer Crop Farmer Butcher Hunter Cook Cleaner  Labourer Trader Teacher Professional/Business Student  Child/Pupil Housewife Retired Unemployed  Other_____________________________(specify) | | | |

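### Control screening for endemic-area exposure rests on one yes/no item about an undefined area, and no place names are recorded before eligibility is decided

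*Protocol*

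**What the plan says.** The criterion is in Protocol 4.1, Inclusion Criteria, for unexposed controls: "No history of residence, work or visiting in LF endemic zones". Section 4.2 says how it is to be applied: "A questionnaire including past travel/residence/contact information will be used to exclude candidates with possible exposure". That sentence points to the control eligibility check in Appendix 2.

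On area exposure the check has one item, "Have you ever lived, worked or visited in a Lassa-endemic area", where a yes makes the candidate ineligible. The other items cover past Lassa testing, cases in the household, contact with cases outside it, and temperature. The form carries no list of endemic districts or countries.

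The Data collection section fixes the order. Candidates answer the exposure questions first and, "if not excluded based on responses, will be asked to respond to a brief demographic questionnaire". District, chiefdom and village appear only on that second form, as a current residence and a single "Previous Residence" block.

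The rest of the protocol does not draw the boundary. The Introduction calls the disease "endemic in parts of West Africa including Sierra Leone, Liberia, Guinea, Mali and Nigeria", section 2.4 names Kenema District as one hotspot, and section 4.2 describes Freetown as "an area considered outside the LASV endemic zone".

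**The concern.** The candidate is asked to apply a boundary that the protocol never defines. A student in Freetown who grew up in, or once visited, an endemic district without knowing its status can truthfully answer no and be enrolled.

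The other items are a weak safety net. The Introduction says most infections are believed to be mild or sub-clinical (while noting that the evidence for the proportions is thin). A past infection may therefore have left no test result and no known contact with a case. The check has no rodent question, so the area item is its only screen for silent rodent-borne exposure.

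Specificity is one of the two main accuracy measures. Under Sample collection, blood and oral fluid are both tested with the new ELISA, and comparison with assays already in use at the hospital is optional. The controls' unexposed status is thus the only guaranteed evidence of true negativity that does not come from the new assay itself.

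**Working it through.** **1. Promise against form.**

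| Information | Promised for exclusion (4.2) | On the eligibility check | On the later control questionnaire |
|---|---|---|---|
| Residence | yes | yes/no, area undefined | current and one previous place, named |
| Travel | yes | yes/no (visited), area undefined | none |
| Contact with cases | yes | yes, specific items | none |

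Contact is screened with usable questions. Residence and travel are screened only through the candidate's own classification. The one source of named places comes after the decision, and no step is stated for checking it against 4.1.

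**2. The plan's own figure.** Table 1 gives 68 per group for sensitivity 85% and relative precision 10%. With n = z²(1−p)/(p·r²), z = 1.96, p = 0.85, r = 0.10:

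n = 3.8415 × 0.15 / (0.85 × 0.01) = 67.79, rounded up to 68. This reproduces, and 70 controls is the working number.

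**3. Effect per control, control status as reference.** One positive in 70 costs 1/70 = 1.43 points. Exact (Clopper-Pearson) 95% intervals:

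| Positives of 70 | Specificity | 95% CI |
|---|---|---|
| 0 | 100% | 94.9–100 |
| 1 | 98.6% | 92.3–99.96 |
| 2 | 97.1% | 90.1–99.7 |
| 4 | 94.3% | 86.0–98.4 |

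**4. Range under assumptions.** Let q be the share of enrolled controls who are truly seropositive. The protocol gives no value; 1% to 10% is assumed. True specificity is set at 99.7%, borrowed from the earlier Ebola oral-fluid assay in section 2.2. Sensitivity runs from 85% (planning value) to 97.4% (the Ebola assay).

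Observed specificity = (1−q)·Sp + q·(1−Se). For q = 5% and Se = 85%: 0.95 × 0.997 + 0.05 × 0.15 = 0.9547.

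Chance of enrolling at least one = 1 − (1−q)^70.

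| q (assumed) | Observed specificity | At least one enrolled |
|---|---|---|
| 0 | 99.7% | 0 |
| 1% | 98.7–98.9% | 50% |
| 2% | 97.8–98.0% | 76% |
| 5% | 94.8–95.5% | 97% |
| 10% | 90.0–91.2% | 99.9% |

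**5. Paired blood as reference.** The Data analysis section also speaks of oral fluid compared with blood. A truly seropositive control should then be blood-positive. If oral fluid is positive too, the pair agrees and there is no false positive. The control drops out of the negatives: k such controls leave 70 − k for specificity.

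**The case against.** Several stronger readings are tempting, and the text does not support them.

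- *Travel is never asked about.* It is: the item covers visits, and a yes excludes. What is missing is the names of the places.
- *No rule excludes a control whose later form shows an endemic district.* Section 4.1 is that rule, whichever form reveals the fact. What is missing is a stated step to compare the two.
- *The planned look at antibody-positive controls could not find the error.* It could in part, because residence is on the control questionnaire and phone numbers allow follow-up questions. Visits, and residences beyond the one previous block, would be missed.
- *Specificity will be biased downward.* That holds only where control status is the reference.
- *Promised rodent questions were dropped.* The Data collection wording is "Unexposed participants will be asked a series of questions regarding exposure to LASV hosts and/or cases", so case questions alone satisfy it literally.

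It can also be said for the plan that the questionnaire is interviewer-administered, staff initial an eligibility line on the study checklist, training and supervision are planned, and medical or nursing students are comparatively well informed. A district list may also sit in interviewer instructions that are not shown. All this may reduce the risk, but the protocol requires neither a list nor any probing about places.

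Finally, with 0 of 70 positive the interval already reaches down to 94.9%, so a shift of a few points lies within sampling uncertainty. That is true for small q. It does not make the shift harmless, since the reported estimate and its interval both move and the data cannot fully show why.

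**Conclusion.** The point stands as a screening weakness that should be corrected before controls are recruited. Section 4.2 says travel and residence information will drive exclusion. The form it cites reduces both to one self-classified answer about an undefined area, and the only named places come after the decision.

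The firm figure is 1.4 points of specificity per truly seropositive control who tests positive, given 70 controls and control status as the reference. The wider range in the table rests on an assumed share of seropositive controls and on borrowed accuracy figures, so it is an illustration and not a forecast. A reader might infer that exposed students will certainly enter; the documents cannot show whether any would. The sample size is unaffected.

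**What to change.** Move the residence block of the control questionnaire into the eligibility check and extend it to all places lived in, worked in and visited. Before deciding eligibility, staff compare the entries with a list of endemic areas attached to the form; any match is not eligible under 4.1.

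The list should work by district or chiefdom within Sierra Leone and by affected region in other countries. Whole-country matching would not do: the Introduction counts Sierra Leone among the partly endemic countries, so it would exclude every Freetown student.

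The cost is one revised form, one attached list, a few more minutes per candidate and somewhat more screen failures. The recorded places would also give the planned investigation of positive controls the travel and residence history it now lacks.
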